### Intervention description {11a}

The intervention exists of a recurrence-focused follow-up approach with routine imaging and serial serum tumor marker testing. The follow-up scheme of the RADAR-PANC trial is based on current surveillance guidelines after resection for PDAC as recommended by the National Comprehensive Cancer Network (NCCN) [11]. This intense follow-up scheme was chosen to increase the chance of early diagnosis of disease recurrence. For the first 2 years after surgery, clinical evaluation, serum carbohydrate antigen 19–9 (CA 19–9) testing, and contrast-enhanced CT imaging of chest and abdomen is performed every 3 months.

Follow-up of patients and related procedures (i.e., blood draws, CT scans) in this study can be performed at the participating hospital, referring hospital, or central coordinating hospital. Study-related follow-up is performed at 3, 6, 9, 12, 15, 18, 21, and 24 months after surgery. For the first follow-up evaluation, patients need to be randomized within the first 3 to 4 months post-surgery. Follow-up appointments are made by the trial coordinator in consultation with the treating clinician. If possible, outpatient clinic visits are combined with CT scan appointments; blood samples are obtained simultaneously.

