
## Participant timeline {13}

**Table Tabb:** 

	**STUDY PERIOD**									
	**Enrolment**	**Allocation**	**Post-allocation**							
**TIMEPOINT**	**Preoperative**	**Postoperative**	**3 months**	**6 months**	**9 months**	**12 months**	**15 months**	**18 months**	**21 months**	**24 months**
PACAP or PACOPS registry, TwiCs & PROMs informed consent	X									
Clinical evaluation	X		X	X	X	X	X	X	X	X
Histological evaluation (confirmation PDAC and R0-R1 resection)		X								
Informed consent for study-related surveillance (investigational arm)		X								
Labs: CA 19–9, extra blood sample	X		X	X	X	X	X	X	X	X
CT chest and abdomen	X		X	X	X	X	X	X	X	X
QoL questionnaires^a^	X		X	X	X	X		X		X

^a^The following questionnaires are used: non-disease specific HRQL (EQ-5D-5L), cancer-specific HRQL (EORTC QLQ-C30), tumor-specific HRQL (EORTC QLQ-PAN26), hospital anxiety and depression scale (HADS), worry of progression of cancer scale (WOPS; modified Dutch seven-item version of the six-item english cancer worry scale (CWS))

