### Recruitment {15}

To achieve adequate patient enrolment and reach the target sample size, all centers are encouraged to participate in the current trial. To ensure enrolment of all eligible patients, the study coordinator(s) are in close contact with the local investigators at the participating centers to obtain weekly updates about patients who underwent macroscopically radical PDAC resection. Eligible patients will be contacted by the study coordinators in consultation with the treating clinicians. If an eligible patient is not yet approached for participation in the PACAP or PACOPS project, informed consent for PACAP or PACOPS, including TwiCs and PROMs, will be discussed by the study coordinator(s).

In 2018, 2348 patients were diagnosed with pancreatic cancer in the Netherlands. About 20% (*n* = 470) of these patients underwent macroscopically radical (R0-R1) resection of the tumor. In the Netherlands, all pancreatic resections are performed in centers affiliated with the DPCG, which will all participate in the current study. Based on the current successful enrolment progress, we anticipate that 75% (*n* = 353) of all patients will be registered yearly in the PACAP cohort and that 80% (*n* = 282) of these patients will provide informed consent for the TwiCs design. About 150 patients each year are expected to be included in other studies with a study-specific follow-up, which is an exclusion criterium for the RADAR-PANC trial. This leaves 282 – 150 = 132 patients eligible for randomization in the current study each year. Fifty percent (*n* = 66) of patients will be randomized to a standardized surveillance strategy. We expect that 80% (*n* = 53) of these patients are willing to participate in the intervention arm of the study, with a participation rate of 100% (*n* = 66) in the control arm as a consequence of the TwiCs design. The expected time needed for inclusion of a total of 306 patients (153 patients in each arm) is therefore 28 months. The final analysis will be performed 30 months after the last patient is enrolled.

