
Data on the incidence of PDAC recurrence, compliance to a recurrence-focused surveillance strategy, clinical, and radiological patterns of recurrence, eligibility for treatment of recurrence, administration of recurrence treatment, as well as type of treatment, reasons to refrain from recurrence treatment, and patient tolerance to recurrence treatment (i.e., completion of treatment as planned) will be analyzed and reported using descriptive statistics. Chi-square or Fisher’s exact test are used to compare categorical variables as appropriate. Parametric continuous variables are presented as mean ± standard deviation (SD) and are compared using the Student’s *t*-test. Non-parametric continuous variables are presented as median with interquartile range (IQR) and are compared using the Mann–Whitney *U* test. Patient-reported outcomes at each time point during follow-up will be compared to baseline scores using a generalized linear mixed model approach to assess a difference in patients’ quality of life and worry of cancer recurrence between the trial arms. Scores will be presented as mean (± SD), changes from baseline as mean differences (MD) and estimates will be calculated to represent a difference in MD between groups with corresponding 95% confidence intervals (CI). Minimally important differences (MIDs) for the EORTC QLQ-C30 will be interpreted based on Musoro et al. for available quality of life domains [34]. If not specified, a ≥ 10-point change is considered meaningful. Disease-free survival and post-recurrence survival will be assessed using Kaplan–Meier survival curves and reported as median with 95% CI. The log-rank test will be used to compare groups. Cox proportional hazards model will be used when appropriate. Stratified analyses will be performed regarding pattern of disease recurrence and type of additional treatment. Various baseline parameters (e.g., sex, age, body mass index (BMI), Charlson Comorbidity Index (CCI), ECOG score, postoperative complications, (neo)adjuvant therapy, resectability status, preoperative CA 19–9 values, tumor location, resection margin status, vascular resection, tumor (T) stage, lymph node (N) stage, tumor differentiation, perineural growth) will be collected. The yield of CT surveillance and role of serum tumor marker testing is assessed by calculating diagnostic accuracy values, i.e., sensitivity, specificity, false-positive and false-negative values. Cost-effectiveness is calculated using a Markov model.

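### The quality-of-life arm effect is a plain difference in change from a preoperative score, and some month-3 scores can predate randomisation: surgery does not bias it, but month 3 can be diluted and precision is lost

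*Protocol article*

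**What the plan says.** All references are to the protocol article.

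- **Model and estimate.** Statistical methods {20a}: "Patient-reported outcomes at each time point during follow-up will be compared to baseline scores using a generalized linear mixed model approach". Changes from baseline are summarised as mean differences (MD), and "estimates will be calculated to represent a difference in MD between groups", with 95% confidence intervals. Baseline is not defined for these scores, and how it enters the model is not stated.
- **Thresholds.** The same section uses published minimally important differences (MIDs) for the QLQ-C30 "for available quality of life domains", then adds: "If not specified, a ≥ 10-point change is considered meaningful".
- **Schedule.** In Participant timeline {13}, the row "QoL questionnaires^a" is marked preoperatively and at 3, 6, 9, 12, 18 and 24 months. The postoperative allocation column has no mark. Month 3 stands in the post-allocation block.
- **Randomisation window.** Intervention description {11a}: "For the first follow-up evaluation, patients need to be randomized within the first 3 to 4 months post-surgery". The informed consent section {26a} gives the same window for offering surveillance.
- **Who can join, and when.** Trial design {8} places cohort consent at diagnosis, and the timeline places it before surgery. Recruitment {15}, which describes finding patients from weekly lists of completed resections, says: "If an eligible patient is not yet approached for participation in the PACAP or PACOPS project, informed consent for PACAP or PACOPS" will be discussed by the coordinators.
- **Missing data.** Section {20c} plans multiple imputation of missing baseline data alongside a complete-data analysis.

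**The concern.** The Discussion ranks quality of life as the most important secondary endpoint and names possible harm to it as a main reason for withholding surveillance. The sample size rests on survival alone, so avoidable dilution or noise in this comparison is not covered by any margin.

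The measurement clock starts before surgery, whereas the question starts at randomisation, which may be months later. The gap holds the resection, the recovery and possibly adjuvant treatment. This raises three questions: whether the month-3 score is always a post-randomisation outcome, whether change from so distant a score is an efficient measure, and what a threshold for change describes when the change spans an operation.

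**Working it through.** The article gives no quality-of-life sample size, standard deviation (SD) or power, so there is no figure of the plan's to reproduce. Quantities marked *assumed* are not in the document.

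**1. Timing.** The first surveillance evaluation is at 3 months and randomisation may fall up to 3 to 4 months after surgery. Section {18a} says that questionnaires run at the cohorts' standard time points, so they are not anchored to randomisation. A patient randomised at 3.5 months who answered at 3 months has a pre-randomisation score that the timeline counts as post-allocation. A patient randomised earlier and only *offered* surveillance at 3.5 months does not have this problem: that score is valid under intention to treat.

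**2. Does surgery bias the arm effect?** Let surgery shift the score by s in everyone and surveillance by δ in the intervention arm. The mean change is s + δ with intervention and s with control; the difference is δ. A simulation of 2,000 trials with 153 per arm (*assumed* SD 20, correlation 0.4) agrees:

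| Surgery shift s | True δ | Mean change, intervention | Mean change, control | Difference |
|---|---|---|---|---|
| −5 | 0 | −5.0 | −4.9 | −0.1 |
| −10 | 0 | −10.0 | −10.0 | 0.0 |
| −15 | 0 | −15.0 | −15.0 | 0.0 |
| −10 | −5 | −15.0 | −10.0 | −5.0 |

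The between-arm difference recovers δ whatever the shift. The within-arm changes do not: with no surveillance effect, a surgery shift of 10 points or more takes both arms to the 10-point threshold.

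**3. Dilution at month 3.** Scores given before randomisation cannot differ by arm except by chance. If a share f of month-3 scores is of this kind, the expected contrast is δ(1 − f). For a true 5 points and *assumed* f:

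- f = 10%: 5 × 0.90 = 4.5
- f = 25%: 5 × 0.75 = 3.75
- f = 50%: 5 × 0.50 = 2.5

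This touches one of the six follow-up time points.

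**4. Precision.** With equal variance σ² before and after and correlation r, the per-patient variance is 2σ²(1 − r) for change and σ²(1 − r²) for a baseline-adjusted score. The ratio is 2(1 − r)/(1 − r²) = 2/(1 + r). The equivalent share of patients lost is 1 − (1 + r)/2 = (1 − r)/2.

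| r (*assumed*) | Variance ratio | Equivalent loss |
|---|---|---|
| 0.2 | 2/1.2 = 1.67 | 40% |
| 0.3 | 2/1.3 = 1.54 | 35% |
| 0.4 | 2/1.4 = 1.43 | 30% |
| 0.5 | 2/1.5 = 1.33 | 25% |
| 0.7 | 2/1.7 = 1.18 | 15% |

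**5. Patients consented after resection.** They can lack an observed preoperative score. If an analysis needs one, as a complete-data analysis would, the difference detectable with 80% power is (1.96 + 0.84) × SD × √(2/n). With an *assumed* SD of change of 20, this is 6.4 points at n = 153 per arm. It rises to 6.8, 7.2 and 7.7 points with 10%, 20% and 30% of patients missing. This is lost precision, not bias in itself, because consent to the cohort and questionnaires precedes randomisation.

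**The case against.** The strongest reply is that the arm comparison is sound. The plan reports a between-group difference, and randomisation removes anything that happened before it. **This stands.** A reader might infer that surgery is confounded with surveillance in the arm effect; step 2 shows that it is not.

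A reader might also infer that late-consented patients have no change score and drop out. The document does not support that. Section {20c} imputes missing baseline data, and a mixed model can retain these patients. The article does not say whether the imputation covers questionnaire scores, and the frequency of late consent is unstated.

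Nor is the 10-point rule the main criterion. It is the fallback after published MIDs, it is not tied to individual patients, and the text does not say whether it applies within or between arms.

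On month 3, the sentence in {11a} can be read as requiring randomisation before the first evaluation, and the timeline's label agrees. That reading is possible, but a window reaching 4 months does not secure it for a 3-month questionnaire.

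Finally, baseline definitions and visit windows are often left to an analysis plan, and both estimators are unbiased. The first part is fair: a missing definition is not the complaint. But the article does fix the estimate as a difference in mean change and does label month 3 as post-allocation. Those two statements can be improved with a score the trial already collects.

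**Conclusion.** The point holds as one of efficiency and classification, not of bias from surgery. It is worth correcting for an endpoint of this rank, and it does not threaten the trial's main conclusion.

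- **Month 3:** the contrast is multiplied by 1 − f. The document does not give f, and it may be small.
- **Precision:** the variance ratio is 1.67 to 1.33 for r of 0.2 to 0.5, and 1.18 at r = 0.7. This rests on an assumed r, equal variances, and a model that estimates the difference in change without baseline adjustment, which is what the text describes. If the model already constrains or adjusts for baseline, this part disappears.
- **Thresholds:** a within-arm change read against an MID or the 10-point fallback includes resection and recovery.

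That baseline means the preoperative score is inferred from the timeline; the statistical section does not say so.

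**What to change.** In Statistical methods {20a}:

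1. Define the quality-of-life baseline. Count a questionnaire as an outcome only if it was completed after randomisation. Treat an earlier month-3 score as baseline information, with a mean common to both arms.
2. Estimate the arm difference at each post-randomisation time point in the mixed model, with the preoperative mean constrained equal across arms. This keeps patients who have no preoperative score. Using that score as a covariate is an alternative only if missing values are imputed under {20c}; otherwise those patients are lost.
3. Interpret the MIDs and the 10-point fallback against the between-arm difference. Report within-arm changes as description only.

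Separately, reconcile Trial design {8} and the timeline (consent at diagnosis or preoperatively) with Recruitment {15} (consent sought from patients already resected), and state whether the imputation covers questionnaire scores.

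The cost is wording and slightly fewer month-3 outcome scores. Questionnaire and randomisation dates must be available; the article does not confirm that questionnaire dates are recorded. No new data collection is needed if they are.

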**Fig. 2 Fig2:**
[figure not shown]
Kaplan–Meier curve comparing overall survival between patients with routine follow-up imaging and symptomatic follow-up in the Netherlands between 2014–2019 (unpublished data)

As we expect 80% of patients to accept the experimental intervention offered in the intervention arm of the study, an estimated refusal rate of 20% needs to be taken into account. This leads to a decrease of the overall survival to 29.4 months (80% × 32.0 months + 20% × 19.0 months) for patients in the intervention arm. Moreover, despite that current non-standardized follow-up in daily clinical practice mainly results in a symptomatic follow-up approach without routine imaging, data from our recurrence database showed that 85/1580 patients (5%) did nonetheless receive routine follow-up imaging based on shared-decision making (the remaining 199/284 patients (70%) who received routine follow-up imaging participated in a clinical study with a study-specific follow-up including routine imaging). This results in a slight increase of the suspected overall survival in the control arm to 19.7 months (95% × 19.0 months + 5% × 32.0 months). The clinically relevant survival difference of 29.4 months vs. 19.7 months for the intervention and control arm, respectively, also approximates the mean survival difference of 9.5 months presented in the meta-analysis from Halle-Smith et al. [33]. These numbers correspond to a relative hazard (RH) of survival of 1.49, which is used to calculate the sample size of the study. Furthermore, as we expect a minimal level of loss to follow-up in this surveillance study, a censoring rate of 1% is expected each month.

To detect a 49% overall survival improvement (RH of survival 1.49) for patients in the intervention group, as compared with the control group, with a statistical power of 80% and a 0.05 two-sided significance level, a sample size of 306 patients is required. This calculation was based on the assumption of an exponential model, a median overall survival of 19.7 months in the control arm, a follow-up duration of 30 months, a drop-out rate of 1% and a baseline event rate of 3.5%. Following this calculation, we plan to include 306 patients in total: 153 patients in the recurrence-focused follow-up group and 153 patients in the non-standardized, symptomatic follow-up group.

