In addition, it was discussed whether the main endpoint should be overall survival, defined as the interval between the date of resection and the date of death, or post-recurrence survival, defined from the date of recurrence diagnosis until date of death. The date of recurrence diagnosis, however, is highly dependent on the applied surveillance strategy and post-recurrence survival will therefore be subjected to lead time bias. Another outcome that was taken into consideration as potential main endpoint was quality of life. One of the most important reasons to refrain from recurrence-focused surveillance is the negative impact it might have on the quality of life of patients with an already poor prognosis. Nevertheless, a sample size can be calculated more reliably by using a hard endpoint such as survival instead of a soft outcome as quality of life. We therefore decided to make quality of life the most important secondary endpoint. In addition, this will be the first study to investigate the impact of a recurrence-focused surveillance strategy on the quality of life of patients after PDAC resection. As previous studies and relevant numbers on this subject are lacking, a proper sample size calculation with quality of life as main study endpoint could not be performed.

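### The quality-of-life arm effect is defined as a difference in change from baseline with no stated baseline adjustment; read that way it is unbiased but less precise than it could be

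*Protocol article*

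**What the plan says.** The section on statistical methods for primary and secondary outcomes {20a} says that patient-reported outcomes at each follow-up time point "will be compared to baseline scores using a generalized linear mixed model approach", in order to assess a difference between the arms. The reported quantities are "changes from baseline as mean differences (MD) and estimates will be calculated to represent a difference in MD between groups", with 95% confidence intervals. MD is the mean change from baseline, so the arm effect is a difference in mean changes. The section names no baseline covariate and no common baseline mean for this model. For overall survival, by contrast, it lists the covariates of the adjusted model.

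The Discussion gives the endpoint its rank: "We therefore decided to make quality of life the most important secondary endpoint". It also explains why no sample size was based on it: "As previous studies and relevant numbers on this subject are lacking, a proper sample size calculation" could not be made with quality of life as the main endpoint. The participant timeline places the baseline questionnaire before surgery and allocation after it.

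**The concern.** A mixed model with baseline as one free time level, and with arm, visit and their interaction, yields exactly the stated contrast. Subtracting the baseline score gives it a weight of one, whatever its correlation with the later score. The efficient weight is the regression slope, which equals rho when the SDs are equal. If rho is low, subtraction adds more noise than it removes.

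A low to moderate rho is plausible here, because resection, and adjuvant therapy in those who receive it, comes between the preoperative score and the follow-up scores. The document gives no figure, so this remains a judgement.

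At stake is the precision of every patient-reported comparison on the top-ranked secondary endpoint. No quality-of-life sample size protects that precision. A difference in change also carries any chance baseline imbalance d into the estimate: with equal SDs it is shifted by (rho−1)d. That averages to zero over randomisations, but it need not be zero in the one trial that is run.

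**Working it through.** **Inputs.** The contrast comes from section {20a}. The document states no SD, correlation or power for quality of life, so there is no figure of the plan to reproduce. The 153 patients per arm were sized for overall survival and serve below only as a ceiling. Rho and the SDs are assumptions, shown over a range.

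**Step 1: variances at one visit, equal SDs.** In units of 2·SD²/n, with n per arm:
- difference in change: 2(1−rho)
- baseline-adjusted, or common baseline mean: 1−rho²
- follow-up score alone: 1

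Information lost = 1 − (1−rho²)/[2(1−rho)] = 1 − (1+rho)/2 = (1−rho)/2.

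| rho (assumed) | change score | adjusted | information lost |
|---|---|---|---|
| 0.1 | 1.80 | 0.99 | 45% |
| 0.2 | 1.60 | 0.96 | 40% |
| 0.3 | 1.40 | 0.91 | 35% |
| 0.5 | 1.00 | 0.75 | 25% |
| 0.6 | 0.80 | 0.64 | 20% |
| 0.9 | 0.20 | 0.19 | 5% |

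Below rho 0.5 the change score has a variance above 1, so it is less precise than ignoring baseline altogether.

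**Step 2: does the mixed model recover the loss?** Generalised least squares with complete data was run for baseline plus one, three and six follow-up visits; six is the number in the participant timeline. The follow-up scores were correlated at 0.6 (at rho where rho was higher). With unconstrained baseline means, the single-visit contrast loses exactly (1−rho)/2 in all three layouts. With one common baseline mean it loses nothing. A simulation of 20,000 trials with 153 per arm and a single follow-up visit compared change scores with baseline adjustment. It gave losses of 34% at rho 0.3 and 25% at rho 0.5 (theory 35% and 25%), and both estimators were centred on the true value of zero.

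**Step 3: unequal SDs.** With k = follow-up SD / baseline SD, the loss is 1 − k²(1−rho²)/(1+k²−2·rho·k).
- k = 1.2: 30%, 18% and 8% at rho 0.2, 0.4 and 0.6. For rho 0.4: 1.44 × 0.84 / (1 + 1.44 − 0.96) = 1.2096/1.48 = 0.817, a loss of 18%.
- k = 1.5: 19%, 8% and 1% at the same rho values.
- k = 0.8: 50% at rho 0.3.

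**Step 4: minimum detectable difference.** At 80% power, two-sided 0.05 and all 153 patients per arm responding, it is 2.80 × √(2/153) = 0.32 SD, multiplied by the square root of the variance in Step 1. Change score against adjusted: 0.41 vs 0.31 SD at rho 0.2, and 0.29 vs 0.26 SD at rho 0.6.

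**Step 5: power illustration, all inputs assumed.** Take SD 22 and 75 responders per arm at month 12. The 75 is built as follows: the planning medians of 19.7 and 29.4 months give 0.5^(12/19.7) = 66% and 0.5^(12/29.4) = 75% alive, about 70% on average; with an assumed 70% response, 153 × 0.70 × 0.70 ≈ 75. For a 10-point difference between arms:
- rho 0.3: SE 4.25 vs 3.43, power 65% vs 83%
- rho 0.5: SE 3.59 vs 3.11, power 80% vs 90%

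The plan uses 10 points only as its fallback threshold for a meaningful change. It is not a design difference between arms.

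**The case against.** The strongest reply is that the text describes how the arm effect is reported, not how baseline enters the model. A difference in mean change can come from a change-score model with baseline as a covariate, which gives the same arm effect as adjusting the follow-up score, or from a model with a common baseline mean. Such details commonly sit in an analysis plan, which is not shown. This stands in part. A reader might infer that the protocol rejects baseline adjustment; it does not, because it excludes neither form. What remains is that the document chooses the comparison and the contrast itself, and the natural reading of that choice is the unadjusted one.

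A reader might also take a loss of 20–40% as established. It is not: that range is the same as assuming rho between 0.6 and 0.2 with equal SDs, and the document supports neither assumption.

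Finally, it can be said that this is only a secondary endpoint, that the confidence intervals remain valid and that the survival analysis is untouched. All of that is correct. It limits the weight of the point, but it is no reason to keep the less precise contrast when the better one costs nothing.

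**Conclusion.** The point holds in conditional form. As written, the quality-of-life contrast is an unadjusted difference in change. It gives up (1−rho)/2 of the information at a single visit with equal SDs and complete data, which is 45% to 5% over rho 0.1 to 0.9. The loss shrinks if follow-up scores are more variable than baseline, grows if they are less variable, and vanishes if baseline adjustment is already intended.

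The cost is precision, together with sensitivity to chance baseline imbalance. A reader might infer systematic bias or loss of a planned power; neither follows. The contrast is unbiased under randomisation, and no power was planned for quality of life. The issue deserves a correction because the endpoint ranks first among the secondary ones and has no sample size of its own. It does not threaten the primary analysis.

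**What to change.** In section {20a}, state that the arm difference at each visit is estimated from a mixed model in one of two forms:

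1. Follow-up scores as outcome, with visit, arm, arm-by-visit, baseline score and baseline-by-visit as fixed effects.
2. All scores including baseline as outcome, with both arms constrained to one common baseline mean. The timeline puts the baseline questionnaire before allocation, so randomisation justifies the constraint. This form also keeps patients whose baseline score is missing.

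Report the adjusted difference per visit with its 95% confidence interval as the arm effect, and keep raw mean changes as description. If one of these models is already intended, a single clause saying so settles the matter.

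The cost is wording only. The baseline score is already collected, and no patients, visits or questionnaires are added. The wording should be fixed before the quality-of-life data are compared by arm.
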